## Abstract

**Background:**

Evidence-based clinical practice guidelines may improve treatment quality, but the uptake of guideline recommendations is often incomplete and slow. Recently new low back pain guidelines are being launched in Denmark. The guidelines are considered to reduce personal and public costs. The aim of this study is to evaluate whether a complex, multifaceted implementation strategy of the low back pain guidelines will reduce secondary care referral and improve patient outcomes compared to the usual simple implementation strategy.

**Methods/design:**

In a two-armed cluster randomised trial, 100 general practices (clusters) and 2,700 patients aged 18 to 65 years from the North Denmark region will be included. Practices are randomly allocated 1:1 to a simple or a complex implementation strategy. Intervention practices will receive a complex implementation strategy, including guideline facilitator visits, stratification tools, and quality reports on low back pain treatment. Primary outcome is referral to secondary care. Secondary outcomes are pain, physical function, health-related quality of life, patient satisfaction with care and treatment outcome, employment status, and sick leave. Primary and secondary outcomes pertain to the patient level. Assessments of outcomes are blinded and follow the intention-to-treat principle. Additionally, a process assessment will evaluate the degree to which the intervention elements will be delivered as planned, as well as measure changes in beliefs and behaviours among general practitioners and patients.

**Discussion:**

This study provides knowledge concerning the process and effect of an intervention to implement low back pain guidelines in general practice, and will provide insight on essential elements to include in future implementation strategies in general practice.

**Trial registration:**

Registered as NCT01699256 on ClinicalTrials.gov.

## Background

The prevalence of low back pain (LBP) in any form is between 25% and 30%. Among LBP patients, about 50% have consulted their general practitioner (GP) for LBP during the last year [1]. LBP generates personal, social, and public costs, and in 2005, Danish costs for treatment, sick leaves, and incapacity benefits were estimated at 16.8 billion DKK (~ 2.3 billion €) [2]. Recently, new clinical practice guidelines were introduced in Denmark, which include advice for primary care on assessment and treatment of LBP patients [3].

The new guidelines are expected to improve overall treatment and they describe the roles of different healthcare providers and define when a GP should refer a patient to a secondary care spine centre. Primary care treatment is considered sufficient for most LBP patients, and secondary referral is usually only recommended if the patient does not improve within eight weeks of primary care treatment. The guidelines include recommendations to the GPs on advising the patients to stay as physically active as possible and to evaluate the need for analgesics and supplementary treatment (*e.g.*, manual therapy or exercises) [3]. More patients are expected to improve by following the guidelines, and referral to secondary care can thus be reduced.

New guidelines are a potential vehicle for changing GP behaviour and securing implementation of evidence-based knowledge into clinical practice. However, implementation strategies with simple, passive diffusion of guidelines, such as simply making newsletters available and other strategies based on information dissemination, have shown insufficient results [4-6]. Consensus regarding the optimal content of components in an intervention strategy has not yet been established, but a review on the effectiveness of clinical guideline implementation suggests the use of a complex approach with active engagement of GPs throughout the process [7]. Activities such as the use of computer-based reminder systems, educational visits, and the use of several activities in combination have shown positive effects in changing GP behaviour [8].

Knowledge concerning how to introduce new guidelines in general practice, however, is sparse, and further knowledge is needed in order to support guideline compliance among GPs and to ensure best evidence-based practice. The aim of this study is to compare a complex implementation strategy with a simple implementation strategy during the implementation of the new LBP guidelines in the North Denmark region. Primary and secondary outcomes pertain to the patient level. A process evaluation pertains to both practice and patient level. A concomitant health economic analysis will be described in a separate protocol.

### Overall theory of changing general practice behaviour

A recently proposed framework for changing clinical behaviour argues that if behaviour change is to be generated, addressing the GP’s capability, opportunity, and motivation is required [9]. The intervention outlined in this study’s protocol supports the GP’s ability to perform an appropriate physical examination and thus enhance GP’s physical capability and thereby support GP’s provision of guidelines. Pop-ups and discussions with guideline facilitators aim to improve the GP’s psychological capability to treat LBP. The practical opportunity for GPs to follow the guidelines is, in our setting, supported through a new referral option for patients with social needs. A social, conducive environment for the process of change is established by conducting practice meetings with guideline facilitators and at small group educational meetings. The GP’s reflective and emotional motivation is addressed through reminders, mouse pads, feedback of monitoring LBP treatment, and discussions with peers and guideline facilitators about the guidelines and the GP’s experiences with the implementation of the guidelines.

Through addressing all of these components, a coordinated set of activities was developed to generate an intervention profile targeted at changing GP behaviour, through better guideline compliance, in order to improve LBP treatment. All activities in this project fall into three categories: capability, opportunity, and motivation (Table 1).

**Table 1 T1:** Activities aimed at changing GP behaviour

**Activities aimed at GPs**	**Capability (physical / psychological)**	**Opportunity (physical / social)**	**Motivation (reflective / automatic)**
**Usual activities (Control and intervention practices)**			
Regional information meetings	X		X
Regional website and written material	X		X
Small group continuing medical education	X		X
**Passive supportive activities (Control and intervention practices)**			
Social medicine referral opportunity		X	
Electronic medical record pop-ups	X		X
Financial incentives			X
Posters reminding of guidelines			X
Mouse pads guiding diagnosis coding, medical record procedures, and reminding of guidelines	X		X
**Pro-active supportive activities (Intervention practices)**			
Facilitator visit	X		X
Feedback/quality assurance	X		X
Info-folder delivered at facilitator visit	X		X
STart Back stratification tool*	X	X	
Social medical screening tool*	X	X	

Activities aimed at changing GP behaviour sorted under capability, opportunity, and motivation. *STarT Back Tool and the SOS screening tool are built into the GPs’ electronic medical record and are filled in at the patient’s first or second consultation regarding LBP.

## Methods/design

### Trial design

This is a two-armed 1:1 cluster randomised controlled trial (CRCT) comparing a control and an intervention group of Danish GP practices. Clusters are defined as patients originating from the same practice. A cluster randomisation was chosen for practical reasons and to prevent possible contamination by asking GPs to treat patients as two groups. The study will include 2,700 patients through stepwise inclusion of 100 practices (Figure 1). In Denmark, almost all secondary-care treatment requires GP referral [10]. All participating GPs receive the usual implementation strategy and passive supportive activities, which include the opportunity to refer patients to an evaluation at the Department of Social Medicine, as well as activities aimed at the inclusion of patients. In addition, intervention practices receive a set of proactive activities including facilitator visits, electronic stratification tools, quality reports, and feedback on LBP treatment.

**Figure 1 F1:**
[figure not shown]
**Chart of expected flow of clusters and patients throughout the trial.** Actual numbers of clusters, average cluster size, and variance of cluster sizes, number of patients contributing data for the primary outcome, as well as number of patients participating with questionnaires will be concluded in reporting of results. ^*^In three practices, single GPs are excluded from participation without excluding the total practice.

Study preparation has been aimed at investigating how to change GPs’ behaviours and how to motivate GPs to participate in the study. Single activities such as new stratification and screening tools in the electronic medical record system, electronic pop-ups, facilitator visits, and patient questionnaires have been tested separately prior to this study. In addition, prior to the study, a full-package test involving installation of pop-ups, GP questionnaires, facilitator visit, and facilitator questionnaire was performed, inspired by the stages in 'Interventions to Change the Physician Performance’ [11] (Table 2). Based on small-scale testing in selected practices, we subsequently adjusted the intervention.

**Table 2 T2:** Stages of the intervention

**Stage**	**Purpose**	**Activities**
**Stage 0: preclinical: model development**	To develop an intervention model based on theoretical understanding and empirical research	In the North Denmark region general practice, a complex strategy for new low back pain guideline implementation will be tested to study behaviour change (professional practice) and clinical results (patient outcomes).
**Stage I: testing and remodelling**	Experiments with activities of the intervention in artificial settings	Testing and remodelling structural medical record changes including GP testing of STarT and SOS with patients. Testing and remodelling different questionnaires on volunteers without LBP, GPs, researchers, and patients. Testing and remodelling LBP patient completed questionnaires. Developing electronic generated feedback quality reports for GPs. Testing and remodelling facilitator visits, and feedback procedures on facilitator training sessions.
**Stage II: maximum variation studies**	Full package intervention in selected units of the target group with close monitoring	Full package delivery of facilitator visit at a general practice, use of stratifying tools and changes in the medical record. Inviting patients to electronic or paper version questionnaire. Monitor whether data imputed in medical records and patient questionnaires will be stored at DAK-E, delivered to external database provider, and available for data retrieval.
**Stage III: efficacy studies**	Cluster RCT with ideal intervention, delivery, randomisation, control group and close monitoring	Randomised controlled trial. Inclusion of provider numbers and patients. Use of guideline facilitator visits. Use of stratifying tools. Use of supervising facilitator contacts and feedback quality reports. Monitoring intervention delivery. Monitoring guideline compliance. Monitoring treatment courses. Monitoring GPs skills and beliefs. Measuring secondary care referral and patient related outcomes.
**Stage IV: effectiveness studies**	Routine intervention delivery and ad hoc or routine monitoring	Cost-effectiveness analysis and other health economic analyses are planned and will be described in a separate protocol.

Stages in study development and for intervention performance.

### Eligibility and recruitment

#### **
*Inclusion and exclusion criteria for general practices*
**

General practices in the North Denmark region are eligible for inclusion. Excluded are practices without the electronic data capture program Sentinel, which links the electronic medical record system to the Danish General Practice Database (DAMD), hosted by the Danish Quality Unit for General Practice (by June 2013, 96% were linked to DAMD). Individual GPs will be excluded if they participated in the pilot testing of the study. By October 2011, the North Denmark region had 191 general practice provider numbers representing 332 GPs. The total number of patients in the North Denmark region was 579,829, giving an average of 3,035 listed patients per practice [12].

#### **
*Recruitment of general practices*
**

At local meetings for GPs, one of the investigators ([name]) informed colleagues about the new guidelines for treatment of LBP and encouraged participation in the study. The GPs will be invited to participate in this study by electronic mail, written letters, and calls from the Quality Unit for General Practice in the North Denmark region (Nord-KAP). To support enrolment, GPs are informed that participation will improve their skills in managing patients with LBP, will help implement the new guidelines, and will provide a new opportunity to refer patients with LBP and concomitant complex social problems to the Department of Social Medicine. In addition, GPs in the control group are paid 1,500 DKK (~200 €) and GPs in the intervention group are paid 2,500 DKK (~333 €) for participation.

#### **
*Inclusion and exclusion criteria for patients*
**

Included are patients aged 18 to 65 years presenting with LBP, with and without leg pain, based on ICPC-2 diagnosis coding L02, L03, L84, or L86 [13]. Excluded are patients with red flags (signs of serious pathology), pregnant women, and patients with insufficient Danish language skills. Excluded patients are registered in DAMD and, together with basic data regarding excluded patients (number, gender, age), will be used to evaluate the selection of patients.

#### **
*Recruitment of patients*
**

For recruiting patients, when a patient with LBP consults a GP, a data-capture program pops up in the electronic medical record. This pop-up contains a question concerning whether the patient agrees to be contacted regarding questionnaire reminders. If the patient agrees, the GP hands out an envelope containing an informational letter about the study, a questionnaire, and a reply envelope with prepaid postage. In the informational letter, patients are encouraged to give informed consent to participate with questionnaires. The consent is given in the first of four questionnaires. Filling in the questionnaire can be done either electronically or by returning the written questionnaire. The general practices will receive posters and mouse pads with LBP diagnoses and pop-up information to remind the GPs of the study. The DAMD database [14] will supply weekly lists of included patients. Reminders will be sent to patients who have agreed to be contacted but who have not filled out a questionnaire. The progress of recruitment will be evaluated every fortnight, and if inclusion is less than one patient per fortnight per participating GP, practices are contacted to discuss reasons for slow inclusion.

#### **
*Implementation activities offered to all participating practices*
**

All practices receive usual guideline implementation, which includes small group continuing medical education meetings, electronic newsletters describing the guidelines [15], and an invitation to participate in regional information meetings. All participating practices are also offered passive supportive activities including restructuring of the electronic medical record, activities reminding of patient inclusion, and the opportunity to refer patients to the Regional Department of Social Medicine for evaluation.

#### **
*Implementation activities offered to intervention practices*
**

In addition to the supportive activities, the intervention practices will receive three additional active supportive activities: guideline for facilitator visit; two patient risk-stratifying tools (Start Back Tool and SOcial risk Screening (SOS) questions; and data feedback on LBP treatment. The following details each of these items:

1. Five primary care physiotherapists are guidelines facilitators. They all have a special certification in LBP assessment and have participated in a ten-hour training course covering the new LBP guidelines in connection with this study. To unify and optimise facilitator visits, the course included lectures and supervised role-playing on how to introduce change in clinical behaviour. The facilitator will visit the practice at inclusion and inform about treatment of LBP according to the new guidelines. Prior to patient inclusion each practice will be offered a one to two hour facilitator visit. After four weeks of patient inclusion, a half-hour follow-up visit or contact by phone or mail will be offered.

2. Two stratifying tools are made available to identify patients at risk of persistent symptoms:

a. The STarT Back Tool divides patients into low, medium, or high risk of prolonged symptoms and guides for treatment [16,17]. In our setting, it is not a requirement that those delivering the treatment for high-risk patients to have specialised training in targeting psychological aspects.

a. The SOS questions (Additional file 1) inquires whether the LBP raises concern about work ability, whether the patient plans to have, or already has, compensation claims or seeks pension, or whether there are any other important issues that could be barriers for recovery. The GPs may use the two risk-stratifying tools at either the initial or the second consultation for LBP. The tools may be viewed in the context of the theory of coloured flags [18] and incorporate biological, psychological, and social aspects. Patients with red flags (serious pathology) are excluded. Yellow flags (beliefs, emotional responses, and pain behaviour) are addressed in the STarT Back Tool. Blue flags (perceptions about the relationship between work and health), black flags (system or contextual obstacles such as legislation, injury claim conflicts, etc.), and orange flags (psychiatric factors) are encompassed in the SOS questions.

3. Feedback on assessment, treatment, and referral of LBP patients during the project: The GPs have access to their own statistics regarding guideline compliance from the DAMD database and may choose to discuss the statistics with their guideline facilitator.

### Data collection

Collected data for this project will be kept and merged by an external provider using the unique personal identification number (CPR number) that is assigned to all Danish citizens. Data are collected from the guideline facilitators, pop-ups in the GPs electronic medical record (DAMD database), GP questionnaires, patient questionnaires, and regional registries (Figure 2).

**Figure 2 F2:**
[figure not shown]
**Illustration of the monitoring procedure.** The first column depicts purpose of measuring; the second column classifies type of measurement; the third column describes type of actions included for measuring; and the fourth column depicts original data storage. All data are merged to the study database.

### Data capture from the medical record pop-ups

The pop-ups for this project are built into the medical record systems and are activated when the GP enters an ICPC-2 code for LBP [14]. The pop-up at the initial consultation includes questions concerning duration of pain, previous LBP episodes, triage (unspecific LBP, nerve root pain, and red flags/serious pathology), and new appointments. At succeeding consultations, the pop-ups contain questions on symptoms, recommended and applied supplementary treatment, and future planned GP visits. The SOS questions and the STarT Back Tool only appear for the intervention practices and can be filled in either at first or second consultation. Every consultation contains a pop-up question on whether the patient has been referred to secondary care treatment (primary outcome). Pop-ups will cease to appear 12 weeks after the first consultation.

### Patient questionnaires

Patients who wish to participate with questionnaires are requested to fill in a questionnaire immediately after the initial GP consultation and after four, eight, and 52 weeks. In case the patient does not respond to a questionnaire, reminders are sent following one- and two-week delays. In the first questionnaire, patients are asked for baseline characteristics on educational level, co-morbidity, as well as the STarT Back Tool questions. Included in the first questionnaire and repeated in the next three questionnaires are questions on the secondary outcomes and about advice received and advice followed.

### Regional registries, facilitators, and GPs

Data regarding provider numbers and associated GPs will be delivered by the Primary Care Unit in the North Denmark region. The regional Department of Health Planning and Quality provide data on primary care reimbursements (*i.e.*, visits to GPs, physiotherapists, and chiropractors).

Following the initial visit and at later contacts with the intervention clinics, the guideline facilitator will log on to the project database and fill out a questionnaire to record which components of the intervention were delivered (Table 3).

**Table 3 T3:** Registrations from facilitators

**Topics at the initial guideline facilitator visit**	**Only intervention group practices**	
	**Answer**	**Appearance of textbox when answering no.**
Medical history	Yes/No	√
Clinical examination	Yes/No	√
Triage	Yes/No	√
ICPC-coding	Yes/No	√
Patient general advices	Yes/No	√
Re-evaluation	Yes/No	√
STarT Back Tool	Yes/No	√
SOcial Screening questions	Yes/No	√
Supplementary treatment	Yes/No	√
Referral to secondary care	Yes/No	√
Guideline hand-outs	Yes/No	√
Pop-up instructions	Yes/No	-
(If yes) – at the computer screen	Yes/No	-
Duration of visit	Minutes	-
Participants	Numbers	-
Follow-up appointment made	Yes/No	√

Overview of data collection from facilitator visits. The questions are entered into the database by the facilitator after the initial visit. Data concerning dates and topics in following contacts between facilitators and practices will be entered as well.

At inclusion and after six months, GPs are asked to fill out a questionnaire. They are asked about their capability, opportunity, and motivation for LBP treatment and their views on implementation strategies.

### Data completeness, quality, and security

Every fortnight, the study group will perform evaluations of the number of included patients, as well as completion and accuracy of data forms, and act on any problems (missing data, slow inclusion, etc.). Data completeness regarding referral to secondary care treatment (primary outcome) is expected to be between 98 and 100%. Data completeness from patient questionnaires (secondary outcomes) is expected to be about 80%. Paper-version questionnaires will be double keyed into the database. Pop-up data are sent daily to the DAMD database, and from the DAMD to the project database on a weekly basis. The project database is provided with access login and writing recording. Backup copying will be performed daily.

### Primary outcome

The primary outcome measure is GP referral to secondary care within 12 weeks after initial GP appointment. A 5% lower referral rate is considered clinically relevant and is expected in the intervention group compared to the control group. To validate if GPs secondary-care referral results in actual secondary care treatment, data is collected from the North Denmark region administration on diagnoses.

### Secondary outcomes

Changes from baseline to four, eight, and 52 weeks are evaluated for the following secondary outcomes: physical function, evaluated by the 23-questionnaire Roland Morris Patrick (for the individual patient, a three-point improvement is considered clinically relevant); pain score, evaluated by a numerical rating scale from 'no pain’ to 'maximal pain’ (score 0 to 10; a 30% change is considered clinically relevant for an individual patient); health-related quality of life, evaluated by EQ-5D score; patient satisfaction (treatment; a 30% change is considered clinically relevant for an individual patient); patient satisfaction (outcome; a 30% change is considered clinically relevant for an individual patient); employment status (have work, yes/no); and sick leave (number of days).

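### Satisfaction is evaluated as change from a first questionnaire completed after the initial consultation, so any part of the satisfaction effect already present by then is subtracted

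*Protocol article*

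**What the plan says.** Under Secondary outcomes the protocol article states: "Changes from baseline to four, eight, and 52 weeks are evaluated for the following secondary outcomes". Both satisfaction items are in the list, each with an individual-level relevance threshold, for example "patient satisfaction (treatment; a 30% change is considered clinically relevant for an individual patient". No exception is made for them.

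The section Patient questionnaires fixes when the first value is taken: patients are "requested to fill in a questionnaire immediately after the initial GP consultation and after four, eight, and 52 weeks". It confirms that this is the reference value: "Included in the first questionnaire and repeated in the next three questionnaires are questions on the secondary outcomes". For non-responders, "reminders are sent following one- and two-week delays". Under Recruitment of patients, the form is handed over during the consultation: "the GP hands out an envelope containing an informational letter about the study, a questionnaire, and a reply envelope with prepaid postage". No measurement before the consultation is described.

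On the start of the intervention, the section on activities for intervention practices says: "Prior to patient inclusion each practice will be offered a one to two hour facilitator visit". That section and the one on medical record pop-ups add that the STarT Back Tool and the SOS questions appear only in intervention practices and may be completed at the first or the second consultation.

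The Statistics section assigns satisfaction to a linear mixed effects model with a practice random effect, in profile analyses. It does not say which contrast carries the result.

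**The concern.** A change score compares arms fairly when its starting value is taken before the arms can differ. Here it is not. The facilitator visit covers what a GP does in a consultation (Table 3 lists history, examination, triage and patient advice), and it is offered before the first patient is included. A patient who then rates satisfaction with treatment is rating a consultation that allocation may have shaped. The first questionnaire even asks about advice received, so the plan itself uses it to record that consultation.

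Subtracting this value removes whatever between-arm difference already exists. A gain in satisfaction that begins at the first visit and lasts would be understated. In the extreme it would disappear from the change comparison although patients in one arm were more satisfied throughout.

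**Working it through.** **Plan's own figure.** The article gives no sample size, SD, effect or correlation for satisfaction. Its 1,321 per group concerns referral. It reproduces as 1,139 per group (18% against 13%, two-sided 5%, 90% power, continuity correction) × 1.16 = 1,321.2. This has no bearing on the point, except that it shows the 16% cluster effect was used as a 1.16 inflation factor.

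**Order of events in an intervention practice.**
1. The facilitator visit is offered.
2. The patient attends the first consultation, where the tools may be used.
3. The GP hands over the questionnaire.
4. The patient completes it, at once or after reminders at one or two weeks.

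The first satisfaction value comes at step 4.

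**Expected estimates.** Let d be the between-arm difference in satisfaction at follow-up, f the share of d already present at the first questionnaire, and ρ the correlation between first and follow-up values, with equal SDs.
- Follow-up level: d
- Change from first value: d − f·d = d(1 − f)
- Follow-up adjusted for first value: d(1 − ρf)

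**Illustration. The values of f, d and ρ are assumptions.**
- Patients per arm: 2,700 / 2 = 1,350.
- Effective number: 1,350 × 0.80 (expected questionnaire completeness) / 1.16 = 931. This assumes that the inflation used for referral also suits satisfaction.
- Take the d that gives a level comparison 90% power: (1.960 + 1.282) × √(2/931) = 0.150 SD.
- SD of change: √(2(1 − ρ)), which is 1.00 at ρ = 0.5.
- Example at f = 0.5, ρ = 0.5: the difference in change is 0.075, its standard error is √(2/931) = 0.0463, and the ratio is 1.62. Power is Φ(1.62 − 1.96) = 37%.

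| f | Share of d left in change | Power of change, ρ = 0.5 (range for ρ 0.3 to 0.7) | Share of d left after adjustment, ρ 0.3 to 0.7 |
|---|---|---|---|
| 0 | 100% | 90% (78% to 99%) | 100% |
| 0.25 | 75% | 68% (54% to 88%) | 92.5% to 82.5% |
| 0.5 | 50% | 37% (28% to 55%) | 85% to 65% |
| 0.75 | 25% | 12.5% (10% to 18%) | 77.5% to 47.5% |
| 1 | 0% | 2.5% (no effect left) | 70% to 30% |

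The level comparison keeps all of d and 90% power whatever f is. Adjusting for the first value loses less than subtracting it, but still removes part of the effect, so it is not the remedy for satisfaction.

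**Other scales.** For pain, Roland Morris and EQ-5D, f on the consultation day is plausibly near zero and the issue is only precision. The variance of a raw change relative to baseline adjustment is 2(1 − ρ)/(1 − ρ²) = 2/(1 + ρ). That is 1.54, 1.33 and 1.18 at assumed ρ of 0.3, 0.5 and 0.7. It ignores clustering and the repeated-measures model, so it is only a guide.

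**The case against.** The strongest reply is that the Secondary outcomes section describes outcomes while the Statistics section gives the model. A profile analysis carries every time point as a response and can show a difference in level, including at the first questionnaire, so the information need not be lost. The choice of contrast could be left to an analysis plan that is not shown. Part of this stands: the mixed model can deliver the right comparison. But the article does not leave the form of the outcome open. It states change from baseline for all secondary outcomes, and a test of parallel profiles is itself a comparison of changes. Nothing names the level difference as the satisfaction result.

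Other objections limit the point and are accepted:

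- A reader might infer that the satisfaction effect always cancels. That needs f = 1. The documents give no f, and several features suggest it is smaller: the tools may be used at the second consultation, facilitator follow-up comes after four weeks of patient inclusion, and re-evaluation and supplementary treatment come later.
- Satisfaction with outcome can hardly be fully formed just after a first visit, so it is less exposed than satisfaction with treatment.
- A reader might take the 30% figure for a responder analysis. It is an aid to interpretation for the individual patient, and no such analysis is planned.
- A reader might extend the point to all seven secondary outcomes. Late return after reminders could let some early effect into the other scales, but the article does not show that this is common or differs by arm.

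Comparing levels also gives up protection against chance or recruitment differences in satisfaction. That protection is not available from a value that allocation may already have moved. The patient-level covariates listed under Statistics remain usable.

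**Conclusion.** The point holds for the two satisfaction outcomes, mainly satisfaction with treatment. As written, the plan evaluates them as change from a value taken after exposure to the intervention can have begun, which leaves d(1 − f) of the effect. The size depends on f, which the documents do not supply. Under the stated assumptions, power at ρ = 0.5 falls from 90% to 68% if a quarter of the effect is present at the first questionnaire, and to 37% if half is.

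The documents do not support the stronger conclusions that the effect is bound to vanish, that pain, function and EQ-5D are seriously biased, or that the trial's main question is compromised. The primary outcome, referral within 12 weeks, and its sample size are untouched. The wording should be corrected before analysis.

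**What to change.** 1. For satisfaction with treatment and satisfaction with outcome, define the result as the between-arm difference in level at 4, 8 and 52 weeks, estimated in the planned mixed model. Treat the first questionnaire as a further outcome time. Neither subtract nor adjust for its value.
2. Do not interpret the 30% change threshold for satisfaction against the first-questionnaire value.
3. Describe the first questionnaire as post-consultation wherever it serves as baseline.
4. Optional, for pain, Roland Morris and EQ-5D: use the first value as a covariate in place of a raw change score, for precision. The small drawback is that a late-returned first value may absorb part of an early effect.

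A sensitivity analysis limited to promptly returned first questionnaires is not advised, because return time arises after randomisation and selecting on it can itself introduce bias.

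The cost is wording in the protocol or analysis plan. All four questionnaires already carry the items. The article says data collection is continuing and that the researchers analysing the data stay blinded until the analysis is completed, so on that account the change can be made without knowledge of results by arm.
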